### Sample size

The study’s sample size is based on the expected difference of the percentage of patients achieving pain improvement between the new and conventional tonic stimulation patterns.

We assumed that the percentages of pain improvement will be 80% for the new stimulation patterns (DTM or FAST) [15, 17] and 50% for the conventional tonic stimulation pattern [25–28] by reviewing the literature. The required sample size was calculated to be 78 cases with a significance level of 0.05, a power of 80%, and 1:1 allocation. Each group (A, B, C, and D) will enroll 20 cases (40 conventional tonic stimulation and 40 new stimulation patterns in Stim-1). Thus, it is possible to secure a power of 0.8 even with the analysis of Stim-1 alone. In addition, considering the insufficient sample size caused by patient detachment during the research process, it is necessary to expand the target number of cases is 23 in each group, resulting in a total sample size of 92 patients in all groups. Assuming, based on past performance, that there are 2–4 cases enrolled in the SCS trial per month, 24–48 patients are expected to be enrolled annually. Therefore, the target number is expected to be reached in 2 to 4 years.

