### Statistical analysis

The primary analysis will be performed after the completion of the SCS trial of the final registered participant. An analysis of the 12-month follow-up period data will be performed at the completion of the 12-month follow-up after the implantation of the final registered participant. Analyses of the 18- and 24-month follow-up period data will be performed at the completion of 24-month follow-up from the implantation of the final registered participant.

The primary outcome analysis will be as follows. Pain improvement will be compared between each stimulation using logistic regression analysis with explanatory variables of stimulation timing (Stim-1, Stim-2), treatment group (new stimulation patterns, conventional tonic stimulation), pre-VAS score for each stimulation pattern, and interaction between stimulation timing and treatment group. The carryover effect will be examined by testing the interaction terms with a significance level of 10%. If there is no carry-over effect, treatment groups will be compared with a significance level of 5%. If a carryover effect is observed, analysis will be performed with data from Stim-1 only.

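### A 10% carryover pre-test chooses the primary analysis, so the Stim-1 comparison it triggers is not a 5% test

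*Protocol article*

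**What the plan says.** Under Statistical analysis, the protocol article models pain improvement by logistic regression on stimulation timing (Stim-1, Stim-2), treatment group (new or tonic), the VAS before each stimulation, and the timing-by-treatment interaction. It then gives a decision rule: "The carryover effect will be examined by testing the interaction terms with a significance level of 10" per cent. Without a carryover finding, the groups are compared at 5%. With one, "If a carryover effect is observed, analysis will be performed with data from Stim-1 only". No adjusted level is given for either branch, and no patient term is named.

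Under Sample size, the article assumes 80% improvement on the new patterns and "50% for the conventional tonic stimulation pattern". It reports: "The required sample size was calculated to be 78 cases with a significance level of 0.05, a power of 80%, and 1:1 allocation". It plans 40 patients on each type of stimulation in Stim-1 and adds: "Thus, it is possible to secure a power of 0.8 even with the analysis of Stim-1 alone". Enrolment is then raised to 23 per group, 92 in total, so 46 versus 46 in Stim-1. The washout between patterns is one day.

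**The concern.** This is the two-stage crossover procedure, in which the data decide which analysis is primary. The difficulty is the dependence between the two steps. A chance imbalance between the orders in Stim-1 makes the interaction look large, so it triggers the switch. The same imbalance makes the Stim-1 comparison look extreme. A nominal 5% test on the same patients, reached by that route, does not have a 5% error rate.

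At stake is the trial's single primary superiority comparison. Even with no carryover, about one trial in ten would take a branch whose false-positive risk is several times nominal, and a reader of the result could not correct for that afterwards. The pre-test would be worth some cost if it found real carryover reliably, so its detection rate matters too.

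**Working it through.** **1. The plan's own figures.** Take 80% versus 50%, two-sided 5% (sidedness is not stated, but this reproduces the number), 80% power, pooled variance under the null.

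n per arm = [1.960·√(2·0.65·0.35) + 0.8416·√(0.8·0.2 + 0.5·0.5)]² / 0.30² = (1.3221 + 0.5389)² / 0.09 = 38.5, so 39 per arm and 78 in total. This matches.

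Stim-1 power with 40 versus 40 = Φ[(0.30·√40 − 1.3221)/0.6403] = Φ(0.898) = 0.8155. With 46 versus 46 it is Φ(1.113) = 0.867. The stated 0.8 is therefore right for a Stim-1 analysis planned from the outset.

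**2. Why the two steps are linked.** Let T1 and T2 be the new-minus-tonic differences in Stim-1 and Stim-2, each with variance v. Let ρ be the within-patient correlation. The orders are reversed between periods, so Cov(T1, T2) = −ρv. The interaction is I = T1 − T2, with variance 2v(1+ρ), and Cov(T1, I) = v(1+ρ). Hence

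Corr(T1, I) = √((1+ρ)/2),

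which is at least 0.71 for any ρ of 0 or more. The two-period average (T1+T2)/2 is uncorrelated with I, so only the Stim-1 branch is distorted.

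**3. Normal-theory size, no carryover and no treatment effect.** Let c be the probability that the Stim-1 test rejects at 5%, given that the interaction is significant at 10%. Overall error = 0.90 × 0.05 + 0.10 × c. The documents do not give ρ, so a range is shown.

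| ρ | c | overall |
|---|---|---|
| 0 | 25% | 7.0% |
| 0.3 | 32% | 7.7% |
| 0.5 | 37% | 8.2% |
| 0.8 | 46% | 9.1% |

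**4. Binary simulation.** Settings: 40 or 46 per order, 10,000 to 20,000 trials each, latent correlation 0–0.8, no carryover. At 50% response a latent 0.8 is a binary correlation of (2/π)·arcsin(0.8) = 0.59, so the simulated maximum lies below the last row above.

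- Pairing modelled: the pre-test fires in about 10% of trials, Stim-1 then rejects a true null in about 24–42%, and overall error is about 7–9%.
- Pairing ignored, as in a logistic model with no patient term: the nominal 10% pre-test fires in up to about 19%. The treatment test is over-conservative, and overall error is about 4–7%. The triggered Stim-1 test still rejects a true null in roughly a quarter of cases.
- Either analysis fixed in advance, with pairing modelled for the two-period one: error stays near 5%.

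**5. Power at 80% versus 50%, no carryover.** Once falsely triggered, Stim-1 power is about 0.57–0.67 (down to 0.54 with 40 versus 40 and latent correlation 0.85). Power of the whole procedure is about 0.92–0.96. The two-period paired analysis alone has about 0.98 or more.

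**6. Does the pre-test find carryover?** Assume no treatment effect, and that prior new stimulation lowers the tonic response. With the paired analysis, 46 per order and latent correlation 0.3–0.8, a 20-point carryover is detected in only about 30–35% of trials (27–32% with 40 per order). A 10-point carryover is detected in about 14–16% with 40 per order.

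**The case against.** Four points can be made for the plan.

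First, a reader might infer that the rule simply breaks the 5% level. The documents do not support that as an unconditional statement. Taken literally, the model has no patient term, and its overall error stays at about 4–7%. The 7–9% applies when pairing is handled. What stands is that the first figure is held down only by a treatment test that is too conservative, and that the Stim-1 branch is distorted either way.

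Second, a reader might infer that the 0.8 power is wrong. It is not. It reproduces, it is stated for Stim-1 alone, and the article does not claim it conditionally on a significant pre-test. Overall power without carryover is above 0.9. When carryover is real, power in the Stim-1 branch can move either way: 0.36–0.60 if a 10–20 point carryover lowers the tonic response, 0.92–0.99 if it raises it.

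Third, the planned adjustment for the VAS before each stimulation was not simulated and might absorb part of a carryover. That is fair. It makes the percentages illustrative, but it does not remove the dependence between the two tests.

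Fourth, the pre-test gives some protection, and always using both periods could be worse. This stands in full. With no treatment effect and a 20–30 point carryover, the two-period analysis rejects in about 34–88% of trials, against 25–44% for the existing rule. At 10 points the two are about equal (12–18% versus 13–19%). The Stim-1 comparison itself is randomised and free of carryover; the fault lies in how the rule selects it.

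**Conclusion.** The concern holds in a limited form. The rule lets a test that is correlated with the Stim-1 result choose the primary analysis, so the Stim-1 branch is not a 5% test: about 24–42% false rejection with no carryover. Overall error is modestly raised, to about 7–9%, if pairing is modelled, and is about 4–7% if it is not. The pre-test also gives poor protection against the moderate carryover that a one-day washout might leave.

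The correlation result is algebraic. The percentages rest on assumed within-patient correlations, on equal order sizes and on omitting the pre-VAS covariate. The sample-size arithmetic is sound. The 0.8 needs only a clarification that it describes a pre-planned Stim-1 analysis and not one reached through the pre-test.

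**What to change.** Delete the pre-test and name one primary analysis at 5%, to be used whatever the interaction shows. There are two defensible choices:

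- **(a) Stim-1 only as primary**, with the two-period analysis as supportive. It is free of carryover, and it is the analysis to which the stated 0.8 applies. The cost is crossover precision. It also has limited slack: missing outcomes count as non-improvement, so if 12 of 92 were missing in Stim-1 the rates would become 0.80 × 80/92 = 0.70 and 0.50 × 80/92 = 0.43, and power with 46 versus 46 would be about 0.72.
- **(b) Stim-1 plus Stim-2 with patient clustering as primary**, with Stim-1 only always reported as a pre-specified sensitivity analysis. Power is about 0.98 or more without carryover. The cost is bias if one day of washout is too short, and a sensitivity analysis beside it does not restore the primary test's error rate.

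Under either choice, report the interaction as an estimate with a confidence interval, together with the change from pre-Stim-1 to pre-Stim-2 VAS by order. Those VAS values are already collected. In the sample-size section, say which analysis the 0.8 describes.

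The change is to wording only. It needs no new data or patients. No interim analysis is planned and recruitment is expected to run to March 2028, so it can be made before the primary data are analysed.

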**Discussion:**

This study aims to clarify the effectiveness of the latest new stimulation patterns compared to the conventional tonic stimulation. In addition, which stimulation pattern is most effective for which kind of causative disease will be clarified.

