### Clinical assessments

On enrollment in this trial, clinical research physicians will obtain information from the patients including age, sex, past history, current medication, causative disease of pain (central post-stroke pain, post–spinal cord injury pain, failed back surgery syndrome, complex regional pain syndrome, post-herpetic neuralgia, diabetic neuropathic pain, peripheral arterial disease, or others), lesion site causing pain (central or peripheral), location of pain (arm, leg, lower back, back, chest, face), laterality of pain (left, right, midline), degree of paralysis (none, mild, moderate, severe), sensory disturbance (hypoesthesia, allodynia, numbness), and duration of disease. During the SCS trial, the degree of pain will be evaluated using a VAS according to the plan (Fig. 1). After SCS system implantation, assessment items will be evaluated according to the plan, including the degree of improvement with respect to pain relief and mental state (Table 2).

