The secondary outcome will be analyzed as follows:Similar analyses of the primary outcome analysis will be performed for each causative disease.Comparison of DTM and FAST stimulation patterns for pain improvement in Stim-3. Pain improvements will be compared between DTM and FAST stimulations using logistic regression analysis adjusted for the treatment group (DTM stimulation, FAST stimulation) and pre-VAS value. Similar analyses will be performed by causative disease.Adjusted mean values and 95% confidence intervals of changes in assessment items including the VAS, SF-MPQ-2, PCS, and QIDS-J before the SCS system implantation, and at 1, 3, 6, 12, 18, and 24 months after SCS system implantation at each time point will be calculated using a linear mixed model with the interaction between treatment group and time point as a fixed effect. Analysis will be performed using a linear mixed model with the change rate and change amount of each indicator as outcome variables. The rate and amount of changes in each index at each evaluation time point will be compared between groups using fixed effects such as pretreatment value of each index, treatment group, evaluation time point, and interaction between the treatment group and evaluation time point. The 12-month analysis will be performed at preoperative, 1, 3, 6, and 12 months, and the 24-month analysis will be performed at 18 months and the final follow-up (24 months).In participants with no missing VAS values preoperatively to 12 months after implantation, analyses of the prognostic factors related to the long-term effect of continuing 33% reduction in the pain VAS over 12 months will be performed using logistic analysis with the following explanatory variables: treatment group, pre-implantation VAS value, sex, age, causative disease, site of pain, degree of paralysis, degree of sensory disturbance, and disease duration.

A comparison between the new and conventional stimulation patterns will be performed with Stim-1and Stim-2. A comparison between DTM and FAST, which is the new stimulation pattern, will be performed with Stim-3. Therefore, this study is designed to compare the VAS improvement rates in different stimulation patterns, so it is not necessary to consider multiplicity.

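### Which pattern suits which disease is to be answered by separate models in up to eight disease groups, with no contrast between diseases and a multiplicity waiver that does not cover them

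*Protocol article*

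**What the plan says.** The Background section makes the choice of pattern by type of neuropathic pain the second clinical question, and the main Discussion repeats it as an aim. The abstract's Discussion states that "which stimulation pattern is most effective for which kind of causative disease will be clarified".

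Clinical assessments lists eight causative-disease categories: seven named diseases plus a class for others. The same section also records "lesion site causing pain (central or peripheral").

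Under Statistical analysis, the primary model is a logistic regression on Stim-1 and Stim-2 with timing, treatment, pre-stimulation VAS and timing-by-treatment. A carryover test at 10% decides whether the analysis falls back to Stim-1 alone. For the secondary outcomes, "Similar analyses of the primary outcome analysis will be performed for each causative disease". The Stim-3 logistic comparison of DTM with FAST is also repeated by disease. No term or test compares the effect between diseases. The section ends by saying that "it is not necessary to consider multiplicity", because new versus tonic uses Stim-1 and Stim-2 while DTM versus FAST uses Stim-3.

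The sample size is set for the overall new-versus-tonic comparison only. The main Discussion marks secondary outcomes (3) and (4) as for reference. Outcomes (1) and (2), which contain the disease-specific analyses, carry no such caveat.

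**The concern.** Asking which pattern works best for which disease is asking whether the pattern effect differs between diseases. Fitting a model in each disease separately does not test that. A significant result in one disease beside a non-significant one in another is not evidence that the effects differ, least of all when the groups are small and of unequal size.

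Two further features make the per-disease results hard to compare. If the carryover test and fallback are repeated within each disease, some diseases will be analysed on two periods and others on one. And the primary-type model pools DTM and FAST, so within a disease it can only rank the new patterns together against tonic. The choice between DTM and FAST rests on Stim-3, where each patient has one or the other.

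The multiplicity argument explains why two overall comparisons do not compete with each other. It does not address running each of them up to eight times. What is at stake is the second clinical question: readers could take a disease-by-disease table as guidance on choosing a device when it carries very little information.

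**Working it through.** **Inputs.** From Sample size: "We assumed that the percentages of pain improvement will be 80% for the new stimulation patterns (DTM or FAST") "and 50% for the conventional tonic stimulation pattern"; 20 evaluable patients in each of four sequence groups (80), raised to 23 (92). From Clinical assessments: eight disease categories. *Assumption:* an even split, because the protocol gives no case mix. This gives 80/8 = 10 to 92/8 = 11.5 patients per disease, taken as 12 below.

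**1. The plan's own figure.** "The required sample size was calculated to be 78 cases with a significance level of 0.05, a power of 80%, and 1:1 allocation". With two-sided alpha and pooled variance under the null, n per arm = [1.960·√(2·0.65·0.35) + 0.842·√(0.8·0.2 + 0.5·0.5)]² / 0.3² = (1.322 + 0.539)² / 0.09 = 38.5. This rounds up to 39 per arm, 78 in total, and matches. At 40 per arm power is 81.6%. The figure is right for the overall comparison.

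**2. Estimability at 12 per disease.** The model has five parameters: intercept, timing, treatment, pre-VAS and interaction. Timing by treatment gives four cells of 6 patients. The chance that a cell is all responders or all non-responders is 0.8⁶ + 0.2⁶ = 0.262 for a new-pattern cell and 2·0.5⁶ = 0.031 for a tonic cell. Treating the cells as independent, at least one such cell occurs with probability 1 − (0.738² · 0.969²) = 0.49. Simulation (24 rows from 12 patients, latent within-patient correlation 0.5) agrees: the five-parameter model separates in about half of datasets (46% to 50% over repeated runs). With the interaction dropped, separation falls to about 8%.

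**3. Power within one disease, 80% versus 50% (Wald tests, same simulation).**

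| Patients in the disease | Data used | Power |
|---|---|---|
| 12 | Stim-1 only | under 0.05 |
| 12 | two periods, interaction dropped | about 0.22 |
| 20 | two periods, interaction dropped | 0.48 |
| 30 | two periods, interaction dropped | 0.72 |
| 40 | two periods, interaction dropped | about 0.84 |

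The normal approximation for two proportions gives 18% for Stim-1 alone at 6 per arm, but it is unreliable at that size. Fisher's exact test gives 3.5%.

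**4. DTM versus FAST within one disease.** This is a parallel comparison at Stim-3, so step 1 applies: 78 patients for a 30-point difference, or 78/92 = 85% of the trial. At 6 per arm the 95% interval has a half-width of 1.96·√(0.41/6) = 0.51, about 51 points.

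**5. Reading across diseases.** Suppose the true advantage is 30 points in every disease. The chance that one disease shows new no better than tonic is 0.082 at 12 per arm and 0.201 at 6 per arm. Over eight diseases this is 1 − 0.918⁸ = 0.50 and 1 − 0.799⁸ = 0.83. Apparent heterogeneity is therefore likely when there is none. Conversely, take two diseases of 12 patients, one with a 30-point effect and one with none. The standard error of the contrast is √(2·0.41/12) = 0.261 with two periods treated as independent and √(2·0.41/6) = 0.370 with one period. Power is then about 21% and 13%.

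**The case against.** *These are secondary analyses, and unadjusted subgroup results are common.* That is so, and the sample size is claimed only for the overall comparison. It would answer the point if the results were called exploratory. Instead the abstract promises an answer, and the caveat in the main Discussion stops at outcomes (3) and (4).

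*Details may sit in an analysis plan that is not shown.* Merging rules, minimum group sizes and penalised fitting may well be there, and their absence is not the complaint. The complaint is about what is stated: separate analyses, a multiplicity reason that does not fit, and a promise of clarification.

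*Case mix may be uneven.* This stands. A reader might infer that no disease can be analysed usefully. The documents do not support that, because a disease with 30 to 40 patients would have reasonable power for pooled new versus tonic. It would do so at the cost of the other diseases, and it would not rescue DTM versus FAST.

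*A reader might infer a flood of false positives.* Nominal arithmetic gives 1 − 0.95⁸ = 34% over eight tests, 1 − 0.95¹⁶ = 56% over sixteen, and 1 − 0.9⁸ = 57% for at least one false carryover signal. These are upper-range values that assume independent tests of exact size. At 12 patients the simulated Wald test of treatment rejects in only 2.7%, 1.1% and 0.2% of null datasets at common response rates of 50%, 65% and 80%. Over eight tests that is about 20%, 9% and 2%. At the protocol's 80% and 50% rates the carryover test fires in about 2% to 3% of datasets, so 1 − 0.98⁸ = 15% to 1 − 0.97⁸ = 22% over eight. The fault is lack of information more than excess false positives.

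*The protocol states no rule for reading results across diseases, nor that the pre-test is repeated within each.* Correct. Both are the natural reading of repeating a similar analysis in order to say which pattern suits which disease, but they are inferences.

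**Conclusion.** The point holds as a should-fix on a stated aim; the primary comparison is untouched. The plan offers no analysis that tests whether pattern effects differ by disease, its multiplicity reason does not extend to repetition over diseases, and the disease results are promised rather than labelled exploratory.

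The numerical part rests on an assumed even split, the protocol's 80% and 50% rates and, in the simulations, a latent correlation of 0.5. The structural fault does not depend on those assumptions: larger groups would improve each estimate, but separate tests would still not compare diseases.

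**What to change.** - In Statistical analysis, assess differences between diseases in one model on all patients that accounts for repeated measures within a patient, with a pre-specified pattern-by-causative-disease interaction. Merge sparse categories in advance. Central versus peripheral lesion site, already collected, is one option, but used alone it answers a narrower question than causative disease.
- Report response proportions and differences for each disease with confidence intervals, as exploratory.
- State that the carryover pre-test and Stim-1 fallback are not repeated within each disease.
- Limit the multiplicity sentence to the two overall comparisons.
- In the abstract's Discussion, say that the disease question will be explored rather than clarified.

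The cost is wording and analysis only, with no new patients or data, and a more modest claim on the second clinical question. The interaction test is itself not strongly powered. For two halves of 46 patients (an assumption) and a 30-point gap in effect, the approximation in step 5 gives about 61% from two periods treated as independent and 36% from Stim-3 alone. The exploratory label is therefore still needed.

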Whereas all SCS devices can provide conventional tonic stimulation, the new stimulation patterns are device-dependent, with each manufacturer providing its own stimulation pattern. This means that only one of the new stimulation patterns can be applied to a patient after SCS system implantation. For this study, a method that makes it possible to apply both DTM and FAST stimulation patterns to one patient during the SCS trial is performed: the Medtronic percutaneous leads are inserted and external state which applies DTM stimulation, and a Boston Scientific cable is connected to the external leads to apply FAST stimulation.

The first clinical question is whether SCS using the latest stimulation patterns for neuropathic pain provides more pain relief than the conventional tonic stimulation. The second clinical question is which kind of stimulation provides the greatest pain relief effect for which kind of neuropathic pain. The hypothesis to be tested in this study is that SCS with the latest stimulation patterns provides significantly more pain relief than the conventional tonic stimulation for patients with neuropathic pain.

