### Study procedures

This trial consists of two steps. The first step is an SCS trial, and the second step is SCS system implantation. In the SCS trial, two cylinder-type leads (Model 977A190; Medtronic Inc.) will be inserted under local anesthesia and connected to an external stimulation device, and intraoperative stimulation will be performed to confirm the area of paresthesia induction. The leads will be placed at vertebral levels of the paresthesia covering the painful area and then directly sutured to the skin at the puncture sites without a skin incision. During the SCS trial, three stimulation patterns, tonic, DTM, and FAST, will be applied. After the SCS trial ends, the inserted leads will be removed in all cases. If pain relief effects are obtained in the SCS trial, the cases will proceed to the second step. More than 1 month after the SCS trial, new cylinder-type leads and an implantable pulse generator (IPG) will be implanted under general anesthesia referring to the previous X-ray of the SCS trial lead placement. The type of implanted devices will be determined as follows: leads (Model 977A190; Medtronic Inc.) and IPG (Intellis; Medtronic Inc.) will be implanted if the DTM stimulation pattern is effective; leads (Linear ST lead; Boston Scientific) and IPG (WaveWriter Alpha 32; Boston Scientific) will be implanted if FAST or tonic stimulation patterns are effective.

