### Method of SCS trial

The SCS trial period will last 9 days and consist of 3 stimulation-on periods and 2 stimulation-off periods (Fig. 1). The initial stimulation will be started one day after SCS lead insertion. The pain relief effect will be assessed using a VAS scale 6 times: pre/post Stim-1, pre/post Stim-2, and pre/post Stim-3. After the assessment of post Stim-3, the SCS leads will be removed. The order of stimulations will be set differently among 4 groups. The order of stimulations is pre-determined for each group and the order of stimulations of each group is shown in Table 1. For example, the order of group 1 will be Tonic stimulation (Stim-1), DTM stimulation (Stim-2), and FAST stimulation (Stim-3). Each stimulation pattern will be performed for 2 days. There will be a 1-day stimulation-off period between each stimulation pattern (Stim-off). The participants will be randomly assigned to one of the 4 groups at the time of study registration. In other words, the order of stimulations is determined when the participants are assigned to the group.

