**Fig. 1 Fig1:**

The schedule of stimulation patterns and timing of pain assessments. The SCS trial period will last 9 days and consist of 3 stimulation-on periods and 2 stimulation-off periods. The initial stimulation will be started 1 day after SCS lead insertion. The pain relief effect will be assessed using a VAS scale 6 times: pre/post Stim-1, pre/post Stim-2, and pre/post Stim-3. After the assessment of post Stim-3, the SCS leads will be removed

**Table 1 Tab1:** The order of stimulations for each group

	Stim-1	Stim-2	Stim-3
Group1	Tonic	DTM	FAST
Group2	DTM	Tonic	FAST
Group3	Tonic	FAST	DTM
Group4	FAST	Tonic	DTM

*DTM* differential target multiplexed, *FAST* fast-acting subperception therapy

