### Secondary outcomes

The following secondary outcomes will be analyzed at the end of the SCS trial: (1) the relationship between causative disease and improvement rates by each stimulation pattern and (2) comparison of the improvement rates between DTM and FAST stimulation patterns in all cases and by causative disease.

After SCS system implantation, the efficacy of SCS is defined as when the VAS value decreases by 33% or more compared to the VAS value before the implantation. Long-term effect is defined as continuing the efficacy of SCS for more than 12 months. The following secondary outcomes will be assessed for six times during 24 months’ follow-up periods after the implantation (Table 2): (3) changes in assessment items including the VAS, SF-MPQ-2, PCS, and QIDS-J preoperatively, and at 1, 3, 6, 12, 18, and 24 months after the implantation; (4) preoperative factors associated with the long-term effects; and (5) adverse events related to this study 3 months after the SCS system implantation. Data will be presented as mean and standard deviation for continuous variables (including VAS score, SF-MPQ-2 score, PCS score, and QIDS-J score).

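### The DTM–FAST comparison uses Stim-3 alone, although every patient receives both patterns in mirror-image order: valid, but inefficient, and the fix is a wording change

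*Protocol article*

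**What the plan says.** The Background section sets the aim: "The second clinical question is which kind of stimulation provides the greatest pain relief effect for which kind of neuropathic pain". Secondary outcome (2) turns this into a "comparison of the improvement rates between DTM and FAST stimulation patterns in all cases and by causative disease".

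Under Study procedures, "During the SCS trial, three stimulation patterns, tonic, DTM, and FAST, will be applied". Table 1 ("The order of stimulations for each group") lists four sequences:
- group 1: tonic, DTM, FAST
- group 2: DTM, tonic, FAST
- group 3: tonic, FAST, DTM
- group 4: FAST, tonic, DTM

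Pain is "assessed using a VAS scale 6 times: pre/post Stim-1, pre/post Stim-2, and pre/post Stim-3" (Method of SCS trial), so a DTM response and a FAST response are planned for every patient.

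The Statistical analysis section nevertheless restricts the analysis: "Comparison of DTM and FAST stimulation patterns for pain improvement in Stim-3", by "logistic regression analysis adjusted for the treatment group (DTM stimulation, FAST stimulation) and pre-VAS value". It repeats the restriction at its end: "A comparison between DTM and FAST, which is the new stimulation pattern, will be performed with Stim-3". The only reason given is that new versus tonic uses Stim-1 and Stim-2 while DTM versus FAST uses Stim-3, from which the section concludes that multiplicity can be set aside. Carryover is not offered as a reason.

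**The concern.** In Stim-3 each patient contributes one record, either DTM or FAST. The comparison is therefore between patients: groups 3 and 4 against groups 1 and 2. The same patients' other new-pattern record, from Stim-1 or Stim-2, plays no part in this question. The design goes to some trouble to give both manufacturers' patterns to one person, and the within-patient contrast that this makes possible is not used.

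At stake is the precision of the comparison that serves the trial's second clinical question. The restriction would be worth its price if it protected against carryover or saved a test, so both possibilities need checking.

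**Working it through.** **The plan's own figure.** Sample size section: 80% vs 50%, alpha 0.05 (taken as two-sided), power 80%, 1:1. With pooled variance and no continuity correction, n per arm = [1.96·√(2·0.65·0.35) + 0.842·√(0.16 + 0.25)]² / 0.30² = 38.5, so 39 per arm and 78 in total, as stated. This figure is for new versus tonic. The protocol states none for DTM versus FAST.

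**Inputs.** N = 80 evaluable (20 per group), or 92 enrolled (23 per group). Assumed, because the protocol does not give them: the within-patient correlation rho (0 to 0.5) and the DTM–FAST difference (80% vs 60%, and 80% vs 70%).

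**Period effects.** With period effects p1, p2 and p3, the within-patient DTM minus FAST contrast carries p2 − p3 in group 1, p1 − p3 in group 2, p3 − p2 in group 3 and p3 − p1 in group 4. The sum is zero, so period effects cancel over the four equal groups.

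**Information.** With per-record variance s²:
- Stim-3 alone: s²/(N/2) + s²/(N/2) = 4s²/N
- within patients: 2s²(1 − rho)/N
- share kept by Stim-3: (1 − rho)/2

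By count, 80 of 160 DTM and FAST records are used at N = 80.

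**Power** (two-proportion normal approximation). The effective n per arm is N/2 = 40 for Stim-3 and N/(1 − rho) for all periods. Example, Stim-3 at 80% vs 60%: (0.20 − 1.96·√(2·0.7·0.3/40)) / √((0.16 + 0.24)/40) = −0.008, which gives 0.497.

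| N = 80 | Share kept by Stim-3 | Power, 80% vs 60% | Power, 80% vs 70% |
|---|---|---|---|
| Stim-3 alone | – | 0.497 | 0.175 |
| All periods, rho 0 | 50% | 0.794 | 0.308 |
| All periods, rho 0.3 | 35% | 0.915 | 0.415 |
| All periods, rho 0.5 | 25% | 0.977 | 0.542 |

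At N = 92 and 80% vs 60%, the figures are 0.554 for Stim-3 against 0.847 to 0.989. The difference from 80% detectable with 80% power at N = 80 is 29 points on Stim-3, against 20, 17 and 14 points at rho 0, 0.3 and 0.5.

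**Check on the binary endpoint.** A simulation of Table 1 (600 trials per setting; logistic model on Stim-3, GEE on the DTM and FAST periods, no pre-VAS) gave variance ratios of about 0.51 at zero correlation, 0.35 at a binary correlation near 0.3, and 0.26 to 0.30 at 0.43 to 0.48. These agree with the formula.

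**Carryover terms.** If first-order carryover terms are added to the all-period model only, Stim-3 keeps 57% at rho 0, 52% at 0.1, 47% at 0.2 and 30% at 0.5. If both models carry them, Stim-3 keeps 29% at rho 0 and 15% at 0.5.

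**Carryover bias.** In groups 1 and 3, Stim-3 directly follows the other new pattern. In groups 2 and 4 it follows tonic, with the other new pattern one period earlier. Take additive first-order carryover cT, cD and cF:
- Stim-3 contrast: (cF + cT)/2 − (cD + cT)/2 = (cF − cD)/2
- all-period contrast: [(cT − cD) − cT + (cF − cT) + cT]/4 = (cF − cD)/4

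Relative to the standard error, the all-period bias is 1/√(2(1 − rho)) times that of Stim-3: 0.71 at rho 0, equal at 0.5 and 1.29 at 0.7.

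**The case against.** The best defence is that nothing is wrong with the Stim-3 test itself. It is randomised, holds period constant, adjusts for pre-VAS, has one record per patient and so no clustering problem, and concerns a secondary outcome with no power claim. The protocol deliberately splits the periods between two questions. This stands: a reader might infer that the comparison is invalid or biased by design, and the document does not support that.

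Three further limits also stand:
- A reader might take the loss to be at least half in all cases. That needs a non-negative rho and no carryover terms fitted only in the larger model. With such terms the loss is 43% at rho 0.
- A reader might conclude that using all periods makes the test well powered. That depends on the assumed difference. The Sample size section assumes 80% for either new pattern, and at 80% vs 70% power stays at or below 0.54 for rho up to 0.5.
- A reader might expect the by-disease comparisons to be rescued. Clinical assessments lists seven named causes plus others. If 80 patients were spread evenly (an assumption), each cause would have about 10, and power for 80% vs 60% would be about 0.10 on Stim-3 against 0.16 to 0.28 over all periods for rho 0 to 0.5. These are rough figures at such small numbers.

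On carryover, the all-period analysis has half the absolute bias under the simple model. Above rho 0.5, however, its bias is larger relative to its standard error, so it needs its own check. Response is measured against each period's own pre-stimulation VAS, which partly addresses residual effects. Both biases vanish if the two new patterns carry over equally.

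What does not stand is the reason given. One DTM–FAST test over all periods is still one test.

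**Conclusion.** The point holds as a matter of efficiency. Stim-3 alone is a sound comparison that leaves 50% (rho 0) to 75% (rho 0.5) of the DTM–FAST information unused, given non-negative correlation and no carryover terms. The Stim-1 and Stim-2 records still serve new versus tonic, including by disease, so the loss concerns the DTM–FAST question only. The restriction buys no protection from carryover, because every Stim-3 record comes after the other new pattern, and it saves no test. The power figures illustrate assumed differences and correlations that the protocol does not give, and they leave out the pre-VAS adjustment. The change is worth making because it is cheap and bears on the trial's second clinical question.

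**What to change.** Reword the DTM–FAST analysis as a GEE or mixed logistic model over all three periods, with pattern (tonic, DTM, FAST), period (Stim-1, Stim-2, Stim-3), the already planned pre-VAS for each period, and clustering on participant. Report the DTM–FAST contrast. Add a carryover check as a sensitivity analysis, for example first-order carryover terms, and keep the Stim-3-only comparison as a second one. Present the by-disease results as estimates with intervals.

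The cost is analysis wording only, with no change to treatment, visits or sample size. Trial status puts the end of recruitment at March 2028, so the change can be fixed by amendment before the analysis. The one downside is that Stim-1 and Stim-2 records would then serve both the primary and this secondary comparison. The sentence that sets multiplicity aside because the periods are separate must be reworded, and the comparison labelled secondary.
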